## Abstract

**Background:**

Annually, about 30% of the persons of 65 years and older falls at least once and 15% falls at least twice. Falls often result in serious injuries, such as fractures. Therefore, the prevention of accidental falls is necessary. The aim is to describe the design of a study that evaluates the efficacy and cost-effectiveness of a multidisciplinary assessment and treatment of multiple fall risk factors in independently living older persons with a high risk of falling.

**Methods/Design:**

The study is designed as a randomised controlled trial (RCT) with an economic evaluation. Independently living persons of 65 years and older who recently experienced a fall are interviewed in their homes and screened for risk of recurrent falling using a validated fall risk profile. Persons at low risk of recurrent falling are excluded from the RCT. Persons who have a high risk of recurrent falling are blindly randomised into an intervention (n = 100) or usual care (n = 100) group. The intervention consists of a multidisciplinary assessment and treatment of multifactorial fall risk factors. The transmural multidisciplinary appraoch entails close cooperation between geriatrician, primary care physician, physical therapist and occupational therapist and can be extended with other specialists if relevant. A fall calendar is used to record falls during one year of follow-up. Primary outcomes are time to first and second falls. Three, six and twelve months after the home visit, questionnaires for economic evaluation are completed. After one year, during a second home visit, the secondary outcome measures are reassessed and the adherence to the interventions is evaluated. Data will be analysed according to the intention-to-treat principle and also an on-treatment analysis will be performed.

**Discussion:**

Strengths of this study are the selection of persons at high risk of recurrent falling followed by a multidisciplinary intervention, its transmural character and the evaluation of adherence. If proven effective, implementation of our multidisciplinary assessment followed by treatment of fall risk factors will reduce the incidence of falls.

**Trial registration:**

Current Controlled Trials ISRCTN11546541.

## Background

Fall incidents are the third cause of chronic disablement in older persons according to the WHO [1]. Annually, about 30% of persons older than 65 years falls at least once and 15% falls at least twice [2-4]. The consequences of falling are severe: 5% of the falls leads to a fracture and 5% of the falls leads to other serious injuries [5,6]. About one in four fallers consults a hospital emergency room or primary care physician after the fall [6]. These facts emphasize the necessity of measures to prevent falling in older persons.

The pathogenesis of falling is multifactorial [2,7]. Causes of falling are impairments in balance, gait, muscle strength, visual acuity and cognition, chronic diseases and use of psychotropic medication [8-12]. Many studies have investigated risk factors of falling [2,13-15] and several risk profiles have been developed [4,14,16-18], which can be used to identify older persons with a high risk of falling.

Interventions to reduce the risk of falling have been successful to a varying degree. Home visits by nurses were found to be ineffective [19], whereas Tai Chi, exercise therapy and multifactorial interventions led to a decrease in falls [20-22]. A meta-analysis showed that a multifactorial fall risk assessment and management programme was effective in all older populations investigated, both with high or low risk of falling [23]. A systematic Cochrane review of preventive interventions showed a positive effect in older persons with a history of falling or in those who were known to have risk factors [24].

The guideline "Prevention of fall incidents in older persons", developed by the Dutch Institute for Healthcare Improvement (CBO), recommends a systematic assessment of fall risk factors in independently living older persons with a high risk of falling. Based on this assessment, a specific and individual treatment plan has been designed [25]. A similar strategy has previously been investigated in the Prevention Of Falls in the Elderly Trial (PROFET) study in the UK, leading to a fall incidence reduction of 50% [13]. However, other studies that evaluated the effectiveness of multifactorial fall prevention strategies were not effective [26-31]. Only one trial studied the cost-effectiveness of a multifactorial intervention program in the USA and reported that the intervention was associated with fewer falls and lower costs [32]. Although many geriatric outpatient clinics have recently started "multidisciplinary fall prevention services", no studies have yet been conducted assessing the effectiveness and cost-effectiveness of such a multifactorial intervention program in older persons with a high risk of recurrent falling.

The objective of this article is to describe the design of a randomised controlled trial that aims to reduce the fall risk in older persons with a high risk of falling. The intervention consists of a systematic assessment of the putative causes of falling and subsequent targeted individualised preventive measures. Unique characteristics of this trial are the evaluation of fall risk factors and subsequent treatment of persons with a high risk of recurrent falling, and the close collaboration between the hospital and primary care physician (transmural care). Both the effectiveness and cost-effectiveness of the intervention will be assessed.

## Method

### Study design and randomisation

This study is a randomised controlled trial (RCT) with a one-year prospective follow-up. Simultaneously, an economic evaluation will be conducted. The Medical Ethics Committee of the VU University Medical Center has approved the study design, protocols and informed consent procedures. Figure 1 shows the design of the study. Potential participants are contacted and after signing informed consent a validated fall risk profile [16] is used to select participants with a high risk of recurrent falling (score of 8 and higher). Participants with a low-risk of recurrent falling are excluded from the RCT. Participants living in a residential home are right away assigned to the high-risk group, which is in accordance with the recommendations of the Dutch Institute for Healthcare Improvement (CBO) guideline [25]. Participants in the high-risk group are blindly randomised into two groups: the intervention group and the usual care group. Prior to the onset of the trial a randomisation schedule is made by a statistician. A block randomisation of 4 per block is used. Using the sequence of this schedule, opaque envelopes are numbered and filled with group names. When a participant is designated to the high-risk group, the interviewer, who is unaware of the content, opens the envelope with the lowest number.

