### Study population

The study population consists of persons of 65 years and over, who consult the Accidents and Emergency Department of the VU University Medical Center (Amsterdam, The Netherlands) or their primary care physician between April 2005 and April 2007 after a fall incident. Inclusion criteria are living independently or in a residential home, living in the vicinity of the VU University Medical Center and having experienced a fall. Exclusion criteria are inability to sign informed consent, inability to provide a fall history, fall due to a traffic or occupational accident, living in a nursing home and acute pathology requiring long-term rehabilitation, such as a stroke.

200 high-risk participants will be included in the intervention study, of which we will enrol 100 participants in the intervention group and 100 in the control group. With a significance level of 0.05, a power of 80% and an expected difference in fall incidence of 50% [13] between the intervention and control group, 57 participants are needed both in the intervention and in the control group. Taking into account a drop-out rate of 30% a minimum of 82 participants are needed in each group. With 100 persons in both the intervention and control group, the numbers are certainly high enough to detect statistical significant differences.

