#### Follow-up

At the first home visit the participants receive a fall calendar [16]. For the period of one year, the participants tick per week whether they did or did not fall during that week. A fall is defined as an unintentional change in position resulting in coming to rest at a lower level or on the ground [41]. Once per 3 months the participants return a calendar sheet by mail. When no sheet is received, or when the sheet is completed incorrectly, we inquire by telephone whether, and if yes, when the participant has fallen in the past 3 months.

The cost-evaluation questionnaire registers the costs made to prevent a new fall or the consequences of a new fall. The questionnaire assesses: the number of visits to physicians, therapists or day care centres; amount and aim of surgical procedures; number of days of admission to a hospital, home or nursing home; purchase of aids and adaptations in the home environment. The questionnaires are conducted 3, 6 and 12 months after the first home visit. The 3 and 6 months questionnaires are sent by mail and apply to the preceding 3 months. The 12 months questionnaire is assessed during the interview of the second home visit. This questionnaire applies to the preceding 6 months. When no questionnaire is received, or when it is completed incorrectly, the questionnaire will be completed by telephone.

During the second home visit, one year after the first visit, the same physical performance tests are conducted along with a reassessment of fall related healthcare costs, medical history, medication use, quality of life and activities of daily living. In addition, in the intervention group, adherence to the treatment regimen is evaluated. Treatment adherence in the intervention group is evaluated per recommendation given. Recommendations regarding changes in medication are evaluated by reassessing the medication use as described above. Adherence to all other recommendations (such as referrals to physical therapy or cardiologist) is assessed by asking whether, to what extent, and how the recommendations of the intervention were effected. The information from the participant is completed with information from the rapports of the involved specialists.

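### Fixed blocks of 4, with envelopes opened by the screening interviewer, make up to one allocation in three foreseeable; the month-12 visit states no safeguard for the performance tests

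*Protocol article*

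**What the plan says.** **Allocation.** Under Study design and randomisation, the protocol article says: "Prior to the onset of the trial a randomisation schedule is made by a statistician". It then gives one block size: "A block randomisation of 4 per block is used". In that order, "opaque envelopes are numbered and filled with group names". On opening it says: "When a participant is designated to the high-risk group, the interviewer, who is unaware of the content, opens the envelope with the lowest number". The Study population section sets the numbers: "we will enrol 100 participants in the intervention group and 100 in the control group".

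**Screening.** The Procedure section has a trained interviewer make the first home visit, at which the risk profile is taken. Under Baseline assessment the profile comprises five questions, two measurements (handgrip strength and body weight) and two interaction items, and a total of 8 or more counts as high risk. Residents of residential homes enter the high-risk group without needing that score. Consent is signed before the profile is taken.

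**Month 12.** The Follow-up section says: "During the second home visit, one year after the first visit, the same physical performance tests are conducted". Of the same visit it says: "In addition, in the intervention group, adherence to the treatment regimen is evaluated". Apart from medication changes, adherence is judged by asking the participant about each recommendation. The performance tests are secondary outcomes. The primary fall outcomes come from a calendar that participants fill in themselves.

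**The concern.** Opaque envelopes and an interviewer unaware of the content protect the envelope that is still sealed. They do not prevent inference from those already opened. With one fixed block length, anyone who tracks the openings knows the place in the block and what remains in it, and here that can be the person whose scoring decides who enters. A screener who expects a particular arm next could, without intending it, let that expectation colour a borderline score. If this happened, the groups could differ at entry in ways that adjustment for age, gender and living situation need not remove.

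The month-12 issue is separate and smaller. Chair stands, walking, reach and standing balance are timed, measured or scored by a tester and depend on effort and encouragement. A tester who already knows the group may score or encourage differently. The adherence questions, asked in one arm only, reveal the group during that visit at the latest.

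**Working it through.** The article gives no figure for predictability, so there is none to reproduce.

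**Inputs.** Block size 4, fixed (Study design and randomisation). Ratio 1:1 and 200 participants (Study population), so 200 / 4 = 50 blocks. A single numbered sequence, with no stratification mentioned. Assumed, because the article does not say: the observer knows or has worked out the block size and has seen all earlier openings.

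**Certain allocations, blocks of 4.** Six orders are equally likely: AABB, ABAB, ABBA, BAAB, BABA, BBAA. An allocation is certain once one arm's two places are used up.
- AABB and BBAA: the last two places are certain, 2 × 2 = 4.
- The other four orders: only the last place is certain, 4 × 1 = 4.
- Total 8 of 6 × 4 = 24 places, or 33.3%. Over 200 participants, 200 / 3 = 66.7, about 67.

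**Best guess, blocks of 4.** Guess the arm with more places left, and toss a coin when they are level.
- Place 1: 1/2.
- Place 2: 2/3.
- Place 3: the first two are alike with probability 1/3 (guess certain) and different with probability 2/3 (coin toss), so 1/3 × 1 + 2/3 × 1/2 = 2/3.
- Place 4: 1.
- Mean (1/2 + 2/3 + 2/3 + 1) / 4 = 17/24 = 70.8%, or about 142 of 200. Chance alone gives 50%.

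**Other block sizes.** The fixed sizes were enumerated exactly. The random sizes were simulated (1,000 trials of 200, each size equally likely), with an optimal guesser who knows which sizes are in use but not the size of each block.

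| Blocks | Certain in advance | Best guess correct |
|---|---|---|
| 4, fixed | 33.3% | 70.8% |
| 6, fixed | 25.0% | 68.3% |
| 8, fixed | 20.0% | 66.6% |
| 4 and 6, random | about 5.5% | about 69.3% |
| 4, 6 and 8, random | about 2.3% | about 68.0% |

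With random sizes of 4, 6 and 8, certain allocations fall from about 67 to about 0.023 × 200 = 4.6, roughly 5 of 200. Correct best guesses fall only from about 142 to 0.68 × 200 = 136. Varying the size removes most of the certainty and little of the better-than-chance guessing.

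**Month 12.** No arithmetic applies. The Follow-up section places three things in one visit: the performance tests, the cost questionnaire on healthcare use, and an adherence review confined to the intervention group. The review goes through each recommendation given, so whoever conducts it has to know that the participant received some. The section does not say who visits, in what order the parts are done, or whether the tester is masked.

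**The case against.** **On allocation.** Being guessable is not the same as being manipulated. Consent comes before scoring, the cut-off is a fixed number, and residential-home participants enter automatically. The article calls the interviewer unaware of the content and does not say that interviewers know the block size or that one person sees every opening. All of this stands. It makes 33.3% and 70.8% upper bounds, and 67 foreseeable allocations are not 67 altered enrolments. It does not remove the point: the article states one block size, an opener who also screens, and a score that the opener measures in part. Handgrip depends on effort and on the tester, so totals near 8 leave some discretion.

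**On month 12.** A reader might infer that the visitor must know the group while testing, so that the tests are assessed unblinded. The article does not say this. Tests done before the adherence questions, or by a second person, would fit its text, and the full protocol may settle the matter. A reader might also think that the description of randomisation as blind is contradicted by the month-12 visit. It is not, because that description concerns allocation only. Nor are the performance tests the only outcomes that could be protected. Staff telephone participants when a calendar sheet or cost questionnaire is missing or wrongly completed, and those callers could be masked too.

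**Conclusion.** The allocation point holds as a weakness in a stated method with an inexpensive remedy. Up to one third of allocations (at most about 67 of 200) could be certain in advance, and up to 71% could be guessed correctly, if one observer knows or infers the block size and has seen all earlier openings. Withheld block size or several interviewers sharing the sequence would lower both figures. The documents allow no estimate of any resulting bias in the fall outcomes, and none is claimed.

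The month-12 point holds only in a limited form: the visitor learns the group at that visit at the latest, and the article states no safeguard for tests measured by that visitor. It bears on secondary outcomes. The calendar-based primary fall outcomes do not depend on the month-12 tester.

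**What to change.** The Progress of the study section has inclusion running to July 2007 and follow-up to July 2008, so both changes could be made for participants still to come.

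1. **Unused envelopes.** Have the statistician replace them with a new sequence in random block sizes, for example 4, 6 and 8, with the sizes not disclosed to the interviewers.
2. **Eligibility before opening.** Require the risk score and the eligibility decision to be in writing, dated and final before an envelope is opened. This step is essential, because varied blocks alone leave best-guess accuracy near 68%.
3. **Second home visit.** Do the performance tests and questionnaires before the adherence form is opened, with the tests first because the cost questions can hint at the group. Keep the allocation off the test form. Where more than one interviewer is available, send one who did not open that participant's envelope.

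**Cost.** A new envelope set, one dated record per participant and a reordered visit form. A different visitor needs no extra staff only if there are at least two interviewers. The statistical downside is a slightly larger possible imbalance: half a block at any stopping point, so up to 4 with blocks of 8 against 2 with blocks of 4, if the switch is made at the end of a block. Sample size, endpoints and treatment are unchanged.

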**Figure 1 F1:**
[figure not shown]
Design of the study.

### Study population

The study population consists of persons of 65 years and over, who consult the Accidents and Emergency Department of the VU University Medical Center (Amsterdam, The Netherlands) or their primary care physician between April 2005 and April 2007 after a fall incident. Inclusion criteria are living independently or in a residential home, living in the vicinity of the VU University Medical Center and having experienced a fall. Exclusion criteria are inability to sign informed consent, inability to provide a fall history, fall due to a traffic or occupational accident, living in a nursing home and acute pathology requiring long-term rehabilitation, such as a stroke.

200 high-risk participants will be included in the intervention study, of which we will enrol 100 participants in the intervention group and 100 in the control group. With a significance level of 0.05, a power of 80% and an expected difference in fall incidence of 50% [13] between the intervention and control group, 57 participants are needed both in the intervention and in the control group. Taking into account a drop-out rate of 30% a minimum of 82 participants are needed in each group. With 100 persons in both the intervention and control group, the numbers are certainly high enough to detect statistical significant differences.

### Procedure

All persons who consult the emergency department or primary care physician after a fall receive usual care. Within two weeks after the initial presentation, written information is sent and several days thereafter, the potential participants are contacted by telephone. All actual participants (who sign informed consent) are visited at their homes by a trained interviewer within 3 months after the fall incident. During the first home visit, the fall risk profile [16], fall history, independence in activities of daily living, quality of life and physical performance are measured. All high-risk participants will report falls during at least one year using a fall calendar and receive a cost-evaluation questionnaire at 3, 6 and 12 months after the first home visit. The times to first and second fall are the primary outcome measures. One year after the first home visit, they are visited a second time to reassess the activities of daily living, quality of life and physical performance. Scores on these questionnaires and tests are used as secondary outcome measures. Furthermore, the treatment adherence and medication use are evaluated. Table 1 presents an overview of the procedure and measurements. The measurements used are described later on in this article.

**Table 1 T1:** Overview of procedure and measurements

	Months	Measurements	Purpose
1st home visit	0	fall risk profile	selection high risk participants
		fall history	assessment of fall risk factors, confounders
		activities of daily living	secondary outcome measure
		quality of life	secondary outcome measure
		medication use	assessment of fall risk factors
		medical history	assessment of fall risk factors, confounders
		physical performance	secondary outcome measure
1st follow-up	3	1st calendar sheet	primary outcome measure
		3 months cost-evaluation	primary outcome measure
2nd follow-up	6	2nd calendar sheet	primary outcome measure
		6 months cost-evaluation	primary outcome measure
3rd follow-up	9	3rd calendar sheet	primary outcome measure
2nd home visit	12	activities of daily living	secondary outcome measure
		quality of life	secondary outcome measure
		medication use	treatment adherence
		medical history	secondary outcome measure, confounders
		physical performance	secondary outcome measure
		treatment adherence	confounder, to enhance the interpretation of the results
4th follow-up	12	4th calendar sheet	primary outcome measure
		12 months cost-evaluation	primary outcome measure

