Fall history is assessed with the fall history instrument (Carefall Triage Instrument, version 007), which is a questionnaire developed by the Academic Medical Center, the VU University Medical Center and the Erasmus Medical Center, The Netherlands. The fall history collects data on the circumstances of the last and previous falls, mobility and risk factors of bone loss and osteoporosis, social status and general health. Medical history is assessed using a questionnaire on self-reported (chronic) diseases both in the past and present. The questionnaire includes 7 major chronic diseases, i.e. chronic lung diseases, cardiac diseases, vascular diseases, stroke, diabetes mellitus, malignant neoplasms and joint disorders (i.e. osteoarthritis and rheumatoid arthritis). In addition, participants are asked to indicate any other chronic disease, including psychological diseases, which they have or have had. Medication use is assessed by directly copying the names of drugs used in the previous two weeks from the containers. The name, doses per unit, number of times taken per day, time of administration, doses per intake, purpose, prescription or over the counter (OTC) and whether the drug has been prescribed after the fall are assessed for each drug. This information is compared to medication records of the public pharmacy. Level of independence in activities of daily living (ADL) will be examined using the Barthel Index (range 0, fully dependent, to 20, fully independent) [33]. The level of functioning on more complex daily activities will be examined using a scale of instrumental ADL introduced by Lawton and Brody (range 0, fully dependent, to 8, fully independent) [34]. Quality of Life (QoL) is examined using the Dutch translations of the SF-12 and the EQ-5D. The SF-12 consists of 12 items and is a abbreviated version of the SF-36 [35]. The SF-12 has been designed and validated to measure health related QoL in large population studies [35,36]. The EQ-5D (EuroQol) has been developed to generate a general index of experienced health and for the assessment of Quality Adjusted Life Years (QALY). It is therefore suitable for economic evaluations [37]. The assessment consists of 5 items (mobility, self-care, usual activities, pain/discomfort and anxiety/depression) and a visual analogue scale (0, worst, to 100, best imaginable health state) [37]. The fall history, ADL and QoL questionnaires are sent to the participants prior to the first home visit. Participants are asked to complete these questionnaires before the home visit. The visiting researcher assists participants who are unable to complete these questionnaires independently.

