### Statistics

Data will be primarily analysed according to the intention-to-treat principle, i.e., including all randomized participants, regardless of whether they received or did not receive the intervention. Subsequently, the results of the intention-to-treat analysis will be compared with the results of an on-treatment analysis.

At baseline, differences in baseline characteristics will be compared between the intervention and control group to examine comparability between the two groups.

To examine the effectiveness of the multidisciplinary transmural care, Cox proportional hazards regression will be conducted, with time to first fall and time to second fall within one year of follow-up as outcome measures, and with age, gender and living situation as covariables. Subsequently, multiple linear regression analyses will be used to compare differences in secondary outcome measures (ADL-score, QoL, physical performance and morbidity data) at 12 months follow-up between intervention and control group.

The economic evaluation will be conducted from a societal perspective, which implies that all costs and outcomes are taken into account. The economic evaluation will involve calculating cost-effectiveness and cost-utility ratios. The incremental costs and effects of the intervention will be compared with usual care. The difference in costs of the intervention group and usual care group will be computed using bootstrapping techniques. Uncertainty ratios will be presented on cost effectiveness and cost utility planes. Acceptability curves will also be estimated. These present the probability that the intervention is cost-effective given a ceiling ratio that policy makers are willing to invest.

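### EQ-5D at months 0 and 12 only: fall-related utility losses that resolve within the year drop out of the QALYs, while their costs are counted

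*Protocol article*

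**What the plan says.** The Baseline assessment section of the protocol article states: "Quality of Life (QoL) is examined using the Dutch translations of the SF-12 and the EQ-5D". It adds that the EQ-5D was developed, among other purposes, "for the assessment of Quality Adjusted Life Years (QALY").

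The Procedure section gives two occasions for quality of life. At the first home visit, "independence in activities of daily living, quality of life and physical performance are measured". At the second, a year later, "they are visited a second time to reassess the activities of daily living, quality of life and physical performance". Table 1 agrees: quality of life appears in the month-0 and month-12 rows and nowhere else.

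Costs follow another schedule. High-risk participants "receive a cost-evaluation questionnaire at 3, 6 and 12 months after the first home visit". The Follow-up section says: "The 3 and 6 months questionnaires are sent by mail and apply to the preceding 3 months"; the 12-month questionnaire covers the six months before it. Resource use is therefore recorded for the whole year. The listed content is visits, surgery, admission days, and aids and home adaptations; no utility item is named. The abstract mentions questionnaires for the economic evaluation at 3, 6 and 12 months without itemising them, but the Procedure and Follow-up sections show that the cost questionnaire is meant.

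The Statistics section commits to the use of both: "The economic evaluation will involve calculating cost-effectiveness and cost-utility ratios", with cost-utility planes and acceptability curves.

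**The concern.** The numerator and denominator of the cost-utility ratio are observed on different footings. An injury in month 2 that has healed by month 12 enters the costs in full, yet neither EQ-5D measurement sees its utility loss. Falls during the year are what the intervention is meant to prevent, and the Background section says that 5% of falls lead to a fracture and 5% to other serious injury. If much of the health loss from such injuries is temporary, the plan measures the saving in cost but only part of the gain in health.

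The schedule is stated in the text and in Table 1, so it is not a detail left to a fuller document. An analysis plan cannot recover utilities that were never collected. Table 1 labels the cost evaluations as primary outcome measures, so the economic evaluation is not a side issue.

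**Working it through.** The article states no QALY figure, so there is none to reproduce. The check compares the true area under an assumed utility path over 12 months with what the EQ-5D schedule would record.

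**Inputs from the article:** EQ-5D at months 0 and 12; cost contacts at months 3, 6 and 12; a further calendar return at month 9.

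**Assumptions, because the article gives no utility values:** a drop of size d at onset; linear recovery over 3 or 6 months, a 4-month block with full recovery, or no recovery; onset uniform over the year; straight lines between measurements (trapezium rule).

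**Single cases with two points.** The recorded loss is half the drop remaining at month 12, times one year.
- d = 0.30, months 2 to 6, full recovery: true 0.30 × 4/12 = 0.10; recorded 0.
- d = 0.30 from month 11: true 0.30 × 1/12 = 0.025; recorded 0.30/2 = 0.15.
- d = 0.20, permanent from month 2: true 0.20 × 10/12 = 0.167; recorded 0.100.
- d = 0.20, permanent from month 10: true 0.20 × 2/12 = 0.033; recorded 0.100.

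These cases show errors in both directions. The mean over onset times is what bears on the comparison of arms.

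**Mean over uniform onset, 3-month linear recovery, per unit drop.**
- Onset before month 9 (share 0.75): true 1.5/12 = 0.125; recorded 0.
- Onset after month 9 (share 0.25): mean true 1.0/12 = 0.0833; mean recorded 0.25.
- True mean: 0.75 × 0.125 + 0.25 × 0.0833 = 0.1146. Recorded mean: 0.25 × 0.25 = 0.0625. Ratio 0.55.

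**6-month linear recovery, per unit drop.**
- True mean: 0.5 × 0.25 + 0.5 × 0.1667 = 0.2083. Recorded mean: 0.5 × 0.25 = 0.125. Ratio 0.60.

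**4-month block, d = 0.30.**
- True mean: 2/3 × 0.10 + 1/3 × 0.05 = 0.083. Recorded mean: 1/3 × 0.15 = 0.05. Ratio 0.60.

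**Permanent loss, per unit drop.** True mean 0.50, recorded mean 0.50, ratio 1.00.

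Comparison of schedules (ratio of recorded to true mean; root mean square error, RMSE, of the individual loss as a fraction of the drop):

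| Recovery | 0/12: ratio, RMSE | 0/3/6/12: ratio, RMSE | 0/3/6/9/12: ratio, RMSE |
|---|---|---|---|
| 3 months | 0.55, 0.164 | 0.95, 0.112 | 0.95, 0.073 |
| 6 months | 0.60, 0.242 | 0.98, 0.121 | 0.98, 0.073 |
| None | 1.00, 0.289 | 1.00, 0.114 | 1.00, 0.072 |

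With two points, 75% of 3-month losses and 50% of 6-month losses are scored exactly zero. With 0/3/6/12 these shares are 25% and 0%; with month 9 added, both are 0%. The ratios do not depend on the size of the drop.

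**The case against.** The schedule itself is hard to dispute, but its consequences are easily overstated.

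- **A reader might infer that two-point QALYs always bias the comparison towards no difference.** The article does not support that. It gives no injury profile, and for permanent losses with uniform onset the mean error is zero. Nor does the measure see only falls close to month 12: the permanent drop at month 2 is still recorded as 0.100 against 0.167.
- **A reader might take the single cases as typical.** They are extremes. Early zeros are partly offset by late overcounting, so the mean shortfall for the 4-month, 0.30 profile is 0.083 − 0.05 = 0.033 QALY per injury, not 0.10.
- **A reader might infer that recovery from the index fall distorts the comparison,** since baseline may be up to three months after it. That path is shared by both randomised arms and largely cancels from the difference, unless the intervention itself changes it. It affects absolute QALYs and noise.
- **The absolute shortfall may be small.** If only the 10% of falls with serious injury carry that profile, and 0.25 to 1 fall per participant is prevented (both assumptions), the missed gain is 0.033 × 0.10 × 0.25 = 0.0008 to 0.033 × 0.10 × 1 = 0.003 QALY per participant. This stands, but a proportional loss in the denominator still moves a ratio, and milder falls may add to it.
- **The straight line is inferred.** The article gives no QALY formula, and weekly fall dates could shape the path. That helps a sensitivity analysis, but the dates carry no utility values.

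**Conclusion.** The point holds as a limitation of the cost-utility analysis that is cheap to reduce. Two EQ-5D measurements miss fall-related losses that begin and end within the year and mis-size those still present at month 12. For assumed temporary losses of 3 to 6 months with uniform onset, about 55–60% of the true mean loss is captured, so a QALY gain from preventing such falls would be understated by a similar proportion. For permanent losses the cost is precision only: an individual RMSE of 0.289 of the drop, against 0.114 with 0/3/6/12.

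These sizes rest on assumed recovery profiles, uniform onset and straight-line interpolation. The article does not show which profile dominates, so an unconditional claim of bias is not supported. Time to first and second fall, the 12-month secondary comparisons, and any cost-effectiveness ratio based on falls are untouched.

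**What to change.** Add the EQ-5D (five items and the visual analogue scale) to the 3- and 6-month cost questionnaires, with the telephone follow-up already planned for non-return. If the burden is acceptable, add it to the month-9 calendar return as well. Without month 9, the interval from 6 to 12 months stays on two points, and a 3-month loss starting at month 8 is still scored zero. State that QALYs are the area under the curve over all available points, with the between-arm difference adjusted for baseline EQ-5D.

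For participants already past those points, keep two-point QALYs, state the limitation, and run a sensitivity analysis that places utility losses at the calendar fall dates. Their size and duration would have to be assumed over a range, or estimated from participants who have the added points.

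The cost is a short form in two or three existing mailings and a small respondent burden. There are two further drawbacks. Early participants will be on a different schedule from later ones, although randomisation in blocks of 4 should spread this evenly over the arms. The added points would also be completed by mail, without the visiting researcher's help that is available at the first home visit. Even with the added points individual values remain approximate: a 0.20 drop at month 2 recovering over 6 months is recorded as 0.067 on 0/3/6/12, against 0.050 true.
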